### Materials

#### Eligibility Screening Questionnaire

We will use an eligibility screening questionnaire, which we developed, to objectively record whether participants meet each item listed in the inclusion criteria. Screening questions pertain to day program schedule attendance, presence or absence of visual impairment, mobility status, presence or absence of cognitive impairment, ability to speak and understand English, and capacity to provide informed consent.

#### Capacity Recording Tool

We will use a capacity recording tool, along with probing questions from a pocket guide for determining a participant’s decision-making capacity [41]. We will use these questions while reviewing the informed consent form to determine whether the prospective participant meets the following criteria: (1) ability to understand relevant information; (2) ability to appreciate the situation and its consequences; (3) ability to reason; and (4) ability to communicate and express a choice. We will determine the participants who meet the 4 criteria to have the capacity to provide informed consent at that time.

#### Demographic Questionnaire

We will use a demographic questionnaire, which we developed, to capture participants’ descriptive information, including age, sex, education level, mobility device use, current exercise participation (ie, how many days per week they engage in exercise, as well as the types of exercise they engage in), current and past (ie, within 12 months) rehabilitation service use for balance impairments (eg, physiotherapy), previous bowling experience, and previous experience using motion-based technologies.

#### MoCA

The MoCA is a brief assessment of global cognitive function [42]. The MoCA assesses individual domains of cognitive function, including attention and concentration, executive functions, memory, language, visuoconstructional skills, conceptual thinking, calculations, and orientation. The MoCA results in scores for the individual cognitive domains that contribute to an overall total. The MoCA is scored out of 30 points, with a score of 25 points or less indicating the presence of cognitive impairment [42]. More specifically, a score of below 23 points on the MoCA indicates MCI [43] and a score of below 17 points indicates Alzheimer disease [44].

#### Mini-BESTest

The Mini-BESTest [40] is a 14-item comprehensive measure that simultaneously assesses several components of balance: anticipatory movements, reactive postural control, sensory orientation, and dynamic gait [45]. To complete the Mini-BESTest, participants are required to perform low-risk activities such as sit to stand, walking at different speeds, standing on a firm surface, and standing on 1 leg. The Mini-BESTest is scored out of 28 points, with higher scores indicating lesser impairments in balance [40]. While there are no prior studies using the Mini-BESTest with people with dementia or MCI, the Mini-BESTest has been shown to have excellent reliability (test-retest and interrater), internal consistency, sensitivity, responsiveness, and validity with populations similar to people with dementia or MCI, such as older adults [46], people with Parkinson disease [47], people with balance disorders [39], and people with chronic stroke [48].

### Intervention Description

We will invite participants to take part in a 10-week motion-based technology intervention (Xbox Kinect bowling), held in a group setting at 4 community-based adult day programs. The intervention sessions will take place twice per week for 10 weeks (20 sessions per site). Sessions will be facilitated by the first author (ED) using teaching techniques successfully employed in previous studies involving motion-based technology and people with dementia or MCI, such as verbal prompts, gesture demonstrations, and physical assistance [37]. During each session, approximately six participants will be seated together in a room and will each have a turn to engage with the technology and game. The facilitator will call upon each participant in the group 1 at a time to take their turn, which will continue for the duration of each session (approximately 60 minutes). While the active player is engaging with the technology, the rest of the group will sit and observe.

The motion-based technology system to be used in this study is the Xbox One Kinect (Microsoft Corporation). We chose the Xbox One Kinect over other commercially available motion-based technology systems (eg, Nintendo Wii) given that interaction with this system requires no handheld controller and relies purely on naturalistic movements (eg, waving an arm). We will used the commercially available bowling game offered through the Kinect Sports Rivals package in the study, alongside the Xbox One Kinect. We chose the Kinect Sports Rivals bowling game given that the game of bowling is generally familiar.

To partake in the intervention, participants are required to rise from their chair, walk to the line (ie, a piece of black electrical tape placed on the floor in front of the technology to cue participants regarding where to stand), play the bowling game, walk back to the chair, and sit down. We will break down the movements required to play the bowling game for participants in a stepwise manner: (1) raise an arm above the head to activate the Kinect sensor; (2) reach the same arm out to the side; (3) close the hand of the extended arm to pick up a bowling ball; (4) extend the same arm back behind to wind up; (5) open the hand of the same arm to release the ball; and (6) swing the same arm forward to throw the ball.

### Environment

We will hold the intervention sessions in the activity room of each adult day program site, which includes a large television set or smartboard, with enough space for participants to sit between turns and to play the game. For consistency, we will configure each day program activity room identically at each site for all intervention sessions, including the placement of the technology, the chairs, the facilitator, and the participants. The facilitator of the intervention sessions will be situated next to the game screen during all sessions to support participants as required. On the days in which video recording occurs, the video cameras will be consistently setup at the front and back of the room during the intervention to capture a comprehensive view of the active players during each of their respective turns.

### Procedure

We will first ask potential participants to complete the eligibility screening questionnaire and the MoCA [42] to ensure that the study inclusion criteria are met. The MoCA will be conducted in person, in a quiet and private setting (ie, in a separate room) at each day program. The first author (ED) will be responsible for administering and scoring the MoCA. At this time, prospective participants will also rereview the informed consent with the researcher, who will then determine their capacity to provide informed consent using the decision-making ability and capacity-probing questions. Once a participant has reviewed the informed consent form to their satisfaction, they will be asked to sign the informed consent form in the presence of the researcher, provided that they have the capacity to independently provide informed consent. Given that decisions are time specific, we will review each participants’ capacity to consent on an ongoing basis (ie, at each point of interaction). All consent and assent forms will be signed in a quiet and private area at the day program.

Upon providing informed consent (whether through independent consent or substitute decision-maker consent plus participant assent), each participant will complete the demographic questionnaire and the Mini-BESTest [40]. We will complete the pretest measurements as close to the eligibility measurements and to the intervention as possible (ie, within 1-3 days) to ensure that the MoCA (used for eligibility and outcome purposes) and Mini-BESTest scores do not become outdated. We will conduct the Mini-BESTest in an open area (eg, exercise room) at each day program to ensure that there is enough space to perform the test. Additionally, 2 members of the research team will be present during the Mini-BESTest to ensure that participants can safely perform the test. That is, 1 research team member will evaluate the participants’ performance while the other member acts as a spotter.

Once the pretest measures are complete, participants will take part in a 10-week motion-based technology intervention (Xbox Kinect bowling), which will be held in a group setting at each day program. Sessions will be held twice per week for 10 weeks (20 sessions), with each session lasting approximately one hour. At the start of each session, the researcher will provide all participants with a verbal and physical demonstration of how to play the game. Additionally, we will record participant attendance to track how many sessions each participant takes part in over the 10-week intervention period. During weeks 1, 5, and 10 of the 10-week intervention period, we will take video recordings of each participant during the intervention using 2 video cameras to capture physical motions related to movement confidence. Immediately following the completion of the 10-week intervention (ie, within 1-3 days), all participants will complete the posttest measures, that is, the Mini-BESTest and the MoCA, for later comparison (Figure 1).

**Figure 1 figure1:**
[figure not shown]
Study procedure. Mini-BESTest: Mini-Balance Evaluation Systems Test; MoCA: Montreal Cognitive Assessment.

### Data Analysis

#### Inclusion in Data Analysis

We will amalgamate data collected from all 4 adult day programs for analysis and reporting purposes. We will encourage participants to attend as many of the intervention sessions as possible; using an intent-to-treat approach, we will include all participants in the final analysis (with number of sessions as a covariate), regardless of the number of intervention sessions they attended. Participants who miss sessions will still be permitted to participate in the motion-based technology intervention. Makeup sessions for participants who are not able to attend all sessions will not be offered. Participants who miss sessions will be accounted for during the analysis.

#### Analysis of Test and Questionnaire Data

All analyses will follow an intent-to-treat approach, whereby we will base the results of the experiment on all participants recruited to take part in the intervention, and not just those who complete the intervention [49]. This approach to analysis will provide a more reliable estimate of the true effectiveness of the motion-based technology intervention, by reproducing what occurs in real-world settings such as community-based adult day programs. We will handle missing data using multiple imputation, which is the recommended standard for accounting for missing research data when working with people who have dementia [50]. We will include study site and the number of intervention sessions attended by the participants in the statistical model as covariates. These analyses will be conducted using IBM SPSS version 26 (IBM Corporation), using a *P* value of <.05 and a confidence interval of 95%.

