### Participants

We will recruit a convenience sample of 24 people with dementia or MCI from 4 community-based adult day programs. The sample size calculation was based on detecting the minimum clinical important difference of 4.0 points [39] on the primary outcome measure (Mini-BESTest) [40], using an effect size of 0.8, an alpha value of .05, a power value of 80%, and a 2-tailed *t* test. We calculated the estimated sample size to be at least 15 participants, which we increased to 24 participants to allow for 40% attrition. We chose an attrition rate of 40% given that absenteeism and unforeseen events (eg, prolonged illness, moving to long-term care) are common among adult day program clients.

Prospective participants will be required to (1) attend the day program at least twice per week on the days in which the intervention is to be offered; (2) meet the screening criteria for the presence of cognitive impairment (determined by a score of ≤25 on the MoCA); (3) speak and understand English well enough to recognize instructions from the facilitator and respond accurately; (4) not have visual impairment that would prevent the participant to view the game screen; (5) be able to stand and walk, with or without an assistive device (eg, walker), to complete the Mini-BESTest; and (6) have the capacity to provide informed consent, or have a substitute decision maker who can provide informed consent. We will exclude participants who do not meet the above criteria from participating in the study.

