### Limitations

Despite the suggested contributions of the study, the proposed study features several potential limitations. First, there is a high risk of researcher bias given that the first author (ED) will be the one to conduct all pre- and posttest measures (ie, MoCA and Mini-BESTest), facilitate the study intervention with participants, and assist with analyzing participants’ movement confidence data. Thus, we recommend that future intervention studies of this nature be carried out with a larger research team where different members can be responsible for conducting different aspects of the study (ie, 1 person conducts the pre- and posttest measures, 1 person facilitates the intervention, and at least two separate individuals analyze the movement confidence data). However, from an opposite perspective, it could be considered positive that the first author (ED) was involved in all aspects of this preliminary study, in order to comment on feasibility and effectiveness, which can help to inform future studies of a similar nature.

Second, we will recruit participants via self-referral to a study advertisement, which suggests that participants who volunteer to take part in the study may be more keen to improve their balance, movement confidence, and cognitive function, which could influence their willingness to take part in the intervention.

Third, we expect that 40% of recruited participants will not complete the study intervention due to reasons outside of our control (eg, prolonged illness, moving to long-term care).

Fourth, while this study is adequately powered, the sample size is still considered small. However, small sample sizes are common in many rehabilitation studies due to lack of resources, lack of funding, recruitment challenges, and high dropout rates [53].

Fifth, the demographic questionnaire developed for this study does not capture participants’ specific diagnosis (eg, Alzheimer disease) or the number of years since their diagnosis. Indeed, it cannot be ruled out that these demographic variables could impact participants’ level of movement confidence, as well as their ability to improve from the intervention. 

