Broadly, we expect that this research will be relevant to scientific, clinical, and professional audiences. For example, we expect that this research will be relevant to scholarly rehabilitation practice, advocacy, or advancing understanding of occupation (ie, meaningful activity) as a fundamental social determinant of health and well-being for people with dementia or MCI. Understanding the potential impacts of using motion-based technology with people with dementia or MCI can inform future evidence-based, community-based rehabilitation practice. That is, if participants show significant improvements in balance, movement confidence, and cognitive function as a result of partaking in the motion-based technology intervention, there is the potential of motion-based technology systems being incorporated into rehabilitation interventions targeting these outcomes. Additionally, we expect that this study will demonstrate the feasibility of using motion-based technology to deliver task-specific interventions to people with dementia or MCI. This is relevant given that tasks and goals of importance to clients are often used to inform rehabilitation interventions. Finally, this research aims to advocate the inclusion of people with dementia or MCI in rehabilitation science and interventions. We expect that this study will demonstrate the ability of people with dementia or MCI to engage in meaningful activity and emphasize the importance of meaningful activity to support health and well-being of people with dementia or MCI.

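### A one-group pre-post change is worded as effectiveness, and the stated imputation, if done under missing at random, could overstate that change for participants lost through illness or long-term care

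*Protocol article*

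**What the plan says.** - **Design.** The Study Design section describes a within-participants study: one group, two measurement times. The Abstract calls it quasi-experimental.
- **Analysis set and missing data.** Analysis of Test and Questionnaire Data includes everyone recruited under an intent-to-treat label and adds: "We will handle missing data using multiple imputation". Site and session attendance are covariates in the statistical model. The article gives neither the missingness assumption nor the imputation model.
- **Interpretation.** The same section says the intent-to-treat approach will give a "more reliable estimate of the true effectiveness of the motion-based technology intervention". Comparison With Prior Work discusses what would follow if participants improved "as a result of partaking in the motion-based technology intervention".
- **Expected loss.** Limitations expects that "40% of recruited participants will not complete the study intervention due to reasons outside of our control (eg, prolonged illness, moving to long-term care". Participants sets the sample size at 15, "which we increased to 24 participants to allow for 40% attrition", because "absenteeism and unforeseen events (eg, prolonged illness, moving to long-term care) are common among adult day program clients".
- **Posttest.** Procedure plans the posttest for all participants, within days of the last session.
- **Limitations listed.** There are eight: researcher bias, self-referral, attrition, small sample, no diagnosis data, pilot coding of movement confidence, geography and setting, and cultural familiarity with bowling.

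**The concern.** Two things bear on what the study may conclude.

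The first is certain. A single group measured twice yields a change, not an effect. The MoCA used to admit participants (25 or below) also serves as their pretest, so some rise at posttest is expected from regression to the mean alone. Familiarity with either test, and events over ten weeks, add to the change. The article's effectiveness wording passes over this, and the limitations do not mention it.

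The second is conditional. Multiple imputation under missing at random supposes that, given what is observed, people without a posttest changed as those with one did. The article's own examples of why people leave are plausibly linked to worse balance and cognition. Each outcome test is taken only once before departure, so the imputation has little that would reveal a decline. An improvement for all recruited participants could then rest on values borrowed from those who stayed well.

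**Working it through.** **The plan's own figure.** Inputs from Participants: "detecting the minimum clinical important difference of 4.0 points" on the Mini-BESTest, effect size 0.8, two-sided alpha .05, power 80%. The implied SD of change is 4.0 / 0.8 = 5.0. A paired t test (noncentral t) has power 0.790 at n = 14 and 0.821 at n = 15, so 15 is reproduced. Inflating for 40% loss gives 15 / 0.60 = 25. The stated 24 is one short, which is immaterial. With 24 recruited and 15 retained, 9 are lost (37.5%).

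**Size of the imputation problem.** Let f be the fraction with a missing posttest, C the mean change in completers and L the mean change in leavers.

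- All-recruited mean = (1 - f) x C + f x L
- Estimate under missing at random, with nothing observed separating leavers from completers: about C
- Overstatement = f x (C - L)

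C = 4.0 is the target difference. L is not in the documents, so a range is shown.

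| L (assumed) | All-recruited mean, f = 0.40 | Overstatement, f = 0.40 | Overstatement, f = 0.20 |
|---|---|---|---|
| +4 | 0.6 x 4 + 0.4 x 4 = 4.0 | 0 | 0 |
| +2 | 0.6 x 4 + 0.4 x 2 = 3.2 | 0.8 | 0.4 |
| 0 | 0.6 x 4 + 0.4 x 0 = 2.4 | 1.6 | 0.8 |
| -2 | 0.6 x 4 - 0.4 x 2 = 1.6 | 2.4 | 1.2 |

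**Tipping point for a zero mean.** L = -C x (1 - f) / f. At f = 0.40 this is -4 x 0.6 / 0.4 = -6.0, which is 10 points below the completers' gain. With 9 of 24 lost it is -4 x 15 / 9 = -6.7. At f = 0.20 it is -4 x 0.8 / 0.2 = -16.

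**Does the imputation model matter?** It was simulated with 3,000 runs, 24 participants, 9 leavers, SD 5, 20 imputations and Rubin's rules. Completers gained 4.0. Assumed attendance was 1 to 10 sessions in leavers and 14 to 20 in completers, and the baseline covariate was unrelated to change.

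| Scenario | Imputation model | Mean estimate | SD | P < .05 |
|---|---|---|---|---|
| Leavers 0, true mean 2.5 | baseline | 4.0 | 1.3 | 75% |
| | baseline + site | 4.0 | 1.4 | 64% |
| | baseline + site + sessions | 4.1 | 4.0 | 6% |
| Leavers 0, true mean 2.5, slope 0.24 points per session in completers | baseline + site + sessions | 3.0 | 4.0 | 4% |
| Leavers -6.7, true mean 0.0 | baseline | 4.05 | 1.3 | 74% |
| | baseline + site | 4.04 | 1.4 | 63% |
| | baseline + site + sessions | 3.9 | 4.1 | 6% |

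Without attendance in the imputation model, the estimate stays at the completer mean whatever happens to leavers. With attendance, leavers' values are extrapolated to low attendance. The estimate may fall, but its SD roughly triples and significance is rarely reached.

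**The comparator.** No arithmetic applies. Set against the one-group design, each of the eight limitations concerns something else. Researcher bias is the closest, and it addresses who measures rather than the absence of a control.

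**The case against.** The strongest reply is that the imputation half rests on inference. The article does not say missing at random, and it gives no imputation model. Session attendance is a stated covariate, so one cannot say that leavers simply receive the completers' improvement. If attendance is also in the imputation model, the false-positive risk largely disappears and the price is imprecision. Pretest scores, demographics and early video may also inform the imputation. Imputation details and sensitivity analyses may sit in a statistical analysis plan that is not shown, so their absence from the article is not a fault. All of this stands, and the point is therefore conditional.

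A reader might also take 40% as the share of missing posttests. The documents do not support that: Limitations speaks of not completing the intervention, Participants counts absenteeism among the reasons, and the posttest is planned for everyone. The sample size does treat the 40% as lost, so it serves as an upper planning figure.

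On wording, the effectiveness phrase is comparative and describes the intent-to-treat approach, not the imputation. The other phrase is conditional, the hypotheses speak of change after the intervention, and the study is called preliminary. This softens the criticism without removing it. An intent-to-treat set in one group is still no estimate of effectiveness, and the limitations still omit the comparator.

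**Conclusion.** The wording point holds without assumptions: a one-group pre-post design cannot support "more reliable estimate of the true effectiveness of the motion-based technology intervention" or improvement "as a result of partaking in the motion-based technology intervention", and the limitations should say so.

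The imputation point holds if missing at random is assumed and leavers do worse than the observed data predict. If attendance does not pull leavers' imputed values down, with completers at +4.0 and 40% missing, the overstatement runs from 0 (leavers also gain 4) to 2.4 points (leavers lose 2). It is half that at 20% missing. The completer gain is the design target, the leaver values are assumptions, and 40% is an upper figure.

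Two stronger readings are not supported. One is that the planned imputation is known to give leavers the completers' gain, since the imputation model is not stated. The other is that Hypothesis 1 may be claimed only if it survives no change in leavers. The protocol's criterion is statistically significant improvement, and nothing in it singles out that scenario as decisive.

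**What to change.** 1. Replace the two effectiveness phrases with *change from pre to post in an uncontrolled group*.
2. Add the missing comparator to the limitations, naming retest, regression to the mean (notably for the MoCA, which also screens for entry) and time.
3. Keep multiple imputation as the main analysis. State its missing-data assumption and whether session attendance enters the imputation model.
4. Report a delta-adjusted analysis for participants lost through illness or long-term care, with its tipping point. For orientation, the all-recruited Mini-BESTest mean reaches zero when leavers change by about -6 points, if 40% are missing and completers gain 4. Significance would be lost before that, so give that crossing as well.
5. Report missing posttests separately from non-completion of sessions, with reasons, so that the actual missing fraction is visible.

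The cost is a few extra imputation runs, some text edits and a more cautious conclusion. No change to recruitment or data collection is needed, provided reasons for a missing posttest are on file.

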**Methods:**

In this quasi-experimental pre- and posttest design, we will recruit 24 people with dementia or mild cognitive impairment from 4 adult day programs and invite them to play Xbox Kinect bowling in a group setting, twice weekly for 10 weeks. We will require participants to speak and understand English, be without visual impairment, and be able to stand and walk. At pretest, participants will complete the Mini-Balance Evaluation Systems Test (Mini-BESTest) and the Montreal Cognitive Assessment (MoCA). We will video record participants during weeks 1, 5, and 10 of the intervention to capture behavioral indicators of movement confidence (eg, fluency of motion) through coding. At posttest, the Mini-BESTest and MoCA will be repeated. We will analyze quantitative data collected through the Mini-BESTest and the MoCA using an intent-to-treat analysis, with study site and number of intervention sessions attended as covariates. To analyze the videos, we will extract count and percentage data from the coded recordings.

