## Methods

### Study Design

This study will use a standard within-participants design, with measurement at pre- and postintervention (1 group, 2 times).

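### Adjusting the intent-to-treat pre-post test for sessions attended, a post-baseline measure of dose, is unnecessary and can shift the primary test to change at zero sessions, depending on a model and coding the article does not name

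*Protocol article*

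**What the plan says.** The study is a one-group, two-time-point design (Study Design: "standard within-participants design, with measurement at pre- and postintervention (1 group, 2 times"). The covariate is specified in three places:

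- Abstract, Methods: "with study site and number of intervention sessions attended as covariates".
- Inclusion in Data Analysis: "we will include all participants in the final analysis (with number of sessions as a covariate), regardless of the number of intervention sessions they attended".
- Analysis of Test and Questionnaire Data: "We will include study site and the number of intervention sessions attended by the participants in the statistical model as covariates". This section also defines intent-to-treat as basing results on everyone recruited, justifies it by real-world effectiveness, and plans multiple imputation in SPSS.

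Attendance is tracked over the 10-week intervention (Procedure), with at most 20 sessions per participant. Hypothesis 1 (Objective) is a pre-post improvement in balance and sets no condition on attendance. The sample size (Participants) rests on the "minimum clinical important difference of 4.0 points", "using an effect size of 0.8, an alpha value of .05, a power value of 80%, and a 2-tailed" t test, and no covariates are mentioned there.

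The article does not name the form of the model, any covariate-by-time term, any centring, or the attendance level at which the pre-post change is tested.

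**The concern.** Sessions attended arises after baseline. In a study without a control arm, it is the amount of intervention received. The article itself expects absenteeism and prolonged illness, so attendance may also track prognosis.

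The stated question is the average change in all recruited participants, whatever they attended. Conditioning on attendance does not serve that question. In one ordinary form of the analysis it replaces the question with another: how much would someone change who attended no sessions? That is an extrapolation to the edge of the data or beyond it, and an intervention that works through attendance would be expected to show little there. The primary Mini-BESTest test, and the MoCA test built the same way, could then miss a real improvement.

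**Working it through.** **Inputs.** From Participants: target change 4.0 and effect size 0.8, so the SD of change is 4.0/0.8 = 5.0; two-sided alpha .05; 15 evaluable and 24 recruited. From the intervention description: four sites and up to 20 sessions. Assumed, because the article gives no values: attendance of mean 12–16 and SD 3–5, and its relation to change.

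**1. The plan's own figure.** An exact paired t test at d = 0.8 gives power 79.0% at n=14 and 82.1% at n=15, so 15 is reproduced. With 40% attrition, 24 × 0.6 = 14.4, close to 15. With all 24 fully observed, power would be 96.3%.

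**2. Change regressed on raw sessions.** The model is change = a + b × sessions + error. The time test is the test of a, the expected change at zero sessions:

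SE(a) = SD × √(1/n + mean² / Sxx), where Sxx = (n − 1) × SD(sessions)²

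- n=15, attendance 14 (SD 4): Sxx = 14 × 16 = 224; SE = 5 × √(0.067 + 196/224) = 5 × 0.970 = 4.85. The SE of the mean change is 5/√15 = 1.29.
- n=24, same attendance: Sxx = 23 × 16 = 368; SE = 5 × √(0.042 + 196/368) = 3.79, against 5/√24 = 1.02.

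The target also moves. If change is proportional to sessions, b = 4/14 and a = 4 − (4/14) × 14 = 0. If attendance and change correlate at 0.5, b = 0.5 × 5/4 = 0.625 and a = 4 − 0.625 × 14 = −4.75, although the mean change is still +4.

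**3. Simulated rejection rates** (6,000 runs per scenario, mean change 4, SD 5, no site terms):

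| n | Attendance mean (SD) | No sessions covariate | Raw, change unrelated to sessions | Raw, half proportional | Raw, proportional | Centred, unrelated |
|---|---|---|---|---|---|---|
| 15 | 16 (3) | 81.7% | 7.6% | 6.2% | 4.5% | 81.2% |
| 15 | 14 (4) | 82.0% | 11.2% | 6.9% | 4.4% | 81.6% |
| 15 | 12 (5) | 83.0% | 18.2% | 8.1% | 5.4% | 82.7% |
| 24 | 16 (3) | 96.1% | 10.0% | 6.3% | 4.9% | 96.0% |
| 24 | 14 (4) | 96.4% | 17.3% | 8.1% | 4.8% | 96.3% |
| 24 | 12 (5) | 96.4% | 27.4% | 10.3% | 5.6% | 96.5% |

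The no-covariate column is from the unrelated scenario; it barely changes in the others.

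With three effect-coded site terms added, the pattern is the same. At n=15 and attendance 16 (SD 3), power is 7% raw against 79% centred (SE 9.0 against 1.27). At n=24 and attendance 13 (SD 5), it is 21% against 96% (SE 3.3 against 1.0). Under proportional change the raw version rejects in about 5% of runs in both settings.

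**4. Centred sessions.** The intercept is then exactly the mean change. With site already in the model, the extra degree of freedom moves power from 80.5% to 79.7% at n=15 and from 96.1% to 96.0% at n=24. If attendance correlates 0.5 with change, residual variance falls and power at n=15 rises from about 82% to 87–88%.

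**5. Main effects only in a mixed model.** Each participant's session count is the same at both time points, so with complete pairs it cancels from the within-person difference. In a worked example with 24 participants, the time effect was 3.62 (SE 0.87) both without covariates and with sessions and site as main effects. Crossing raw sessions with time gave 3.71 (SE 3.21); crossing centred sessions gave 3.62 (SE 0.89).

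**The case against.** The strongest reply is that the harm comes from a model the article does not name. It specifies covariates and SPSS, not a change-score regression, a covariate-by-time term or raw coding. Such details are commonly left to a fuller document. Multiple imputation yields complete pairs, so the harmless main-effects model is a live possibility. There is no randomised contrast to bias. The article also uses intent-to-treat mainly as an inclusion rule, which it follows.

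Much of this stands. A reader might infer that the planned test has only 5–20% power, that raw and centred coding are the only two possibilities, that a benefit growing with attendance is always removed, or that centring merely wastes a degree of freedom. The documents support none of these. The low power needs a particular model and coding. A third form leaves the time contrast untouched. A centred model keeps the benefit in the time effect and may gain precision.

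What does not fall is the choice itself. Placing attendance in the model is a stated rule given three times, not an omitted detail. It sits beside a hypothesis and a sample size that concern the unconditional mean change.

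**Conclusion.** The point holds in a conditional form. The plan adjusts for a post-baseline measure of dose in an analysis meant to estimate the average change in all recruited participants.

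- **Raw sessions in a change-score or time-crossed model:** the test refers to change at zero sessions. Power falls from about 80% (n=15) or 96% (n=24) to roughly 7–27% if change is unrelated to attendance, and to about 5% if it is proportional.
- **Centred sessions:** the estimate equals the mean change and little is lost; precision may improve.
- **Main effects only, complete-data mixed model:** no effect on the time contrast.

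The planning values are the article's own. The attendance mean, its SD and its relation to change are assumptions. The n=24 figures treat all 24 participants as fully observed, which imputation does not achieve, so they are upper limits. Since attendance is not needed for the stated question in any version, the primary result should not hang on an unstated coding choice.

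**What to change.** Remove sessions attended from the primary Mini-BESTest and MoCA models. Test the mean pre-post change in all recruited participants, adjusted for site only, with site coded so that the time effect is the average over sites.

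Report attendance in a separate exploratory dose-response model, with sessions mean-centred and no causal wording. Attendance may also serve as an auxiliary variable in the multiple imputation already planned.

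The cost is a wording change and one extra exploratory model, with no new data. The downside is a possible small loss of precision compared with centred adjustment if attendance correlates with change: at a correlation of 0.5 and n=15, about 82% power instead of 87–88%. Because the article reports that data analysis is underway, the change should be dated and disclosed with the results.
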